**Fig. 1 Fig1:**
[figure not shown]
Study design. MRI magnetic resonance imaging

All participants will be followed up for 12 months. Informants (usually family members) are recruited, as is usual in cognitive studies, to provide additional data since we expect the sample size to decline over time. Participants, informants, and exercise physiologists are not blinded to the treatment, but all baseline and follow-up assessments (physical, neuropsychological, and radiological) are blinded to treatment allocation. According to data protection rules, all data are anonymised. Technicians involved in statistical analysis will be blinded to treatment allocation.

### Participants

#### Recruitment and study setting

The study is conducted in the University of Lisbon at the Faculdade de Medicina and Instituto de Medicina Molecular in Lisbon, and the Hospital de Santo António, Centro Hospitalar do Porto. The Human Kinetics Faculty (from the University of Lisbon) is a partner of the study. These centres, both urban and academic, have experience in the diagnosis and management of patients with cognitive decline of a vascular aetiology and in stroke care. Subjects are referred to each participating centre directly from the community (participants can be self-presenting, as the study was advertised in public spaces) or from a medical appointment (general family doctor in primary care, or from neurological, mental health, memory clinics, or hospital settings). Participants can be referred to the study due to minor cognitive complaints/symptoms or minor behavioural changes attributed to a cerebrovascular aetiology. Patients can also be referred if they had a previous stroke or transient ischemic attack (TIA), even without complaints, if neuropsychological evaluation showed evidence of any change considered to be due to a cerebrovascular aetiology. Post-stroke cognitive impairment is common even after successful clinical recovery from a stroke episode, and a recent study showed that at least one cognitive domain was impaired in 83% of cases [20]. Considering TIA, more than one cognitive domain was impaired in more than a third of patients 3 months after a TIA [21].

Eligible subjects are contacted by the recruitment team to further explain the procedures of the study and to confirm inclusion and exclusion criteria. Written informed consent is given by participants and informants. This consent allows access to the subject’s clinical records for research purposes and indicates their willingness to participate in all the activities inherent to the study. Those remaining eligible and without contraindications to physical activity are contacted by an investigator and proceed to baseline assessments.

### Inclusion and exclusion criteria

#### Inclusion criteria

Participants are included if they are 18 years and older and fulfil the following criteria: 1) provide written informed consent; 2) are fluent in the Portuguese language; 3) are able to read and write; 4) have an available, reliable informant; and 5) show clinical and functional criteria A and B as below.

Criteria A (any one of the following three):Probable mild cognitive vascular impairment (VCI, no dementia) [22];Previous ischaemic or haemorrhagic stroke (more than 6 months before), with modified Rankin score ≤ 2 at baseline and without formal indication for physiotherapy;TIA (more than 1 month before), diagnosed by a neurologist or with an identified vascular lesion (correlated with TIA clinical symptoms) in cerebral computed tomography (CT)/magnetic resonance imaging (MRI).

Criteria B: No functional changes, i.e. instrumental activity of daily living (IADL) scale = 0 (no item changed, or one single item with minimal change), according to the scoring methods of the LADIS study (minimum of four items applicable) [23] or no cognitive changes regarding the suggested Montreal Cognitive Assessment Test (MoCA) cut-off point for dementia in Portuguese clinical samples (score < 17) [24].

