### Study outcomes

The primary outcome measure will be cognitive decline defined as a dichotomous variable (decline/no decline) through cognitive status criteria as described in the Assessments section below. The secondary outcomes are changes in neurocognitive scores of at least 1.5 standard deviation (SD) from baseline to endpoint (using *z* scores), a decline in the raw values of neuropsychological tests, in quality of life, functional and motor status, and falls.

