**Fig. 2 Fig2:**
[figure not shown]
Study schedule

In all assessments (baseline and follow-up clinical visits), the cognitive status of patients is classified into the following groups: 1) diagnosis of dementia; and 2) diagnosis of cognitive impairment with no dementia according to clinical, neuropsychological, and functional criteria. For this purpose, we used the usual criteria and definitions of the Diagnostic and Statistical Manual of Mental Disorders (edition 4 revised; DSM-4TR) [25]. At baseline, patients could only fulfil VCI without dementia defined as evidence of cognitive impairment and clinical consensus to identify significantly related vascular features; exclusion of dementia when impairments were not sufficiently severe to interfere with social or occupational functioning or when impairments were more focal than the global requirement for a diagnosis of dementia. For follow-up we considered the following criteria for subtypes of dementia: probable Alzheimer disease [26]; probable vascular dementia [27]; subtype of subcortical vascular dementia [28]; frontotemporal dementia [29]; and Lewy body dementia [30]. The criteria for Alzheimer’s disease with a vascular component was made when the investigator judged that the clinical picture presented both aspects of Alzheimer’s disease and vascular dementia.

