### Neuropsychological and quality of life assessments

Cognitive evaluation follows the same protocol in all assessments and is applied by a trained neuropsychologist. It consists of a neuropsychological battery specifically designed for this study in order to be sensitive for vascular cognitive deficits and includes the following tests: The Montreal Cognitive Assessment (MoCA) [34, 35] for general assessment; Letter cancellation [36] and the Wechsler Adult Intelligence Scale-Revised (WAIS-R) Digit Span (forward) [37, 38] for the assessment of attention and concentration; Verbal Fluency [35], Trail-Making Test [39–41], Wechsler Adult Intelligence Scale-3rd edition (WAIS-III), Digit-Symbol [42], and Stroop Test [43, 44] to assess executive functions; the California Verbal Learning Test-9 (CVLT-9) [45, 46], Wechsler Memory Scale (WMS) Visual Reproduction and Logical Memory subtests [36, 47], and WAIS-R Digit Span (backward) subtest [36, 37] to assess memory; and the Alzheimer's Disease Assessment Scale (ADAS) Naming objects and Following Commands subtests [48, 49] to assess language. The impact of cognitive performance on daily living activities is assessed with the Instrumental Activities of Daily Living (IADL) [50]; the presence of depressive symptoms and apathy are assessed using the 15-item Geriatric Depression Scale [51] and the Apathy Evaluation Scale [52, 53], respectively.

The quality of life and other specific measures for the assessment of an individual psychological resources and the economic impact of the disease are also added in this protocol. These measures include the Euro Qol-5 [54] and the Quality of Life in Alzheimer’s Disease (QOL-AD) [55, 56], the 13-item Orientation to Life Questionnaire to measure Antonovsky’s sense of coherence (SOC-13), a health-promoting resource which strengthens resilience where higher scores indicate an ability to adapt to stressful situations [57–59], the Successful Aging Index (SAI) [60], an a priori index model of successful ageing which was validated with respect to service use, and the Resources used in Dementia Interview (RUD) [61] to collect data on resource utilisation to calculate costs of care (healthcare resource utilisation) and time dedicated to caregiving in dementia.

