#### Data analysis

Data will be registered according to the Consolidated Standards of Reporting Trials (CONSORT) guidelines for randomised controlled trials [19]. We will use intention-to-treat analyses as the primary analysis with all participants included according to initial group allocation. For the primary outcome analysis (dependent variable: cognitive decline according to clinical criteria), we will conduct a logistic regression analysis. Since the outcomes are measured at 6 and 12 months, we will fit a generalised estimating equations (GEE) logistic regression model for the data. The models will adjust for covariates which are assumed to interfere with cognition in the follow-up (age, gender, education, and baseline MoCA). For secondary outcomes, logistic or linear regression analysis will be used as applicable.

For each of the outcome endpoints (i.e. transition of cognitive status and change in neuropsychological evaluation through composite or global scores) the change from baseline to 6 months and 12 months will be assessed, even though we will consider 12 months as the primary marker of success.

Observing a statistically significant difference on any of the outcomes will be considered preliminary evidence of efficacy. We will also report variances, co-variances, and effect sizes, as well as sampling feasibility (i.e. ease of recruitment, recruitment rate, withdrawal rate).

The same qualified statistician involved in the statistical analysis designed the SAP and will independently review the analysis according to the plan.

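### The primary model adjusts for baseline MoCA but not for baseline IADL, although function helps define the primary outcome; adding IADL is an optional, nearly free improvement

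*Protocol article*

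**What the plan says.** **Entry.** Inclusion criteria, Criteria B, offers two alternatives. The first is functional: "No functional changes, i.e. instrumental activity of daily living (IADL) scale = 0 (no item changed, or one single item with minimal change"). The second is cognitive: "or no cognitive changes regarding the suggested Montreal Cognitive Assessment Test (MoCA) cut-off point for dementia in Portuguese clinical samples (score < 17").

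**Primary outcome.** Study outcomes defines it as "cognitive decline defined as a dichotomous variable (decline/no decline) through cognitive status criteria". The Assessments section (text under Fig. 2) classifies status at each visit as dementia or as "diagnosis of cognitive impairment with no dementia according to clinical, neuropsychological, and functional criteria". At baseline only impairment without dementia is allowed. One of the two grounds for that is "exclusion of dementia when impairments were not sufficiently severe to interfere with social or occupational functioning"; the other is that deficits are too focal for a dementia diagnosis.

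**Collection.** Neuropsychological and quality of life assessments: "The impact of cognitive performance on daily living activities is assessed with the Instrumental Activities of Daily Living (IADL"), within a battery that is the same at all visits. Baseline assessment precedes randomisation.

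**Model.** Data analysis specifies a GEE logistic regression on the 6- and 12-month outcomes: "The models will adjust for covariates which are assumed to interfere with cognition in the follow-up (age, gender, education, and baseline MoCA"). Baseline IADL is not listed.

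**The concern.** When a binary outcome is a diagnosis with a cognitive and a functional component, the baseline values of both are natural candidates for adjustment. In a logistic model, leaving out a prognostic baseline variable pulls the estimated treatment odds ratio towards 1 and costs some power. The plan takes the baseline value of the cognitive component and leaves out the functional one, although both are used as entry markers and both are on the case report form. Randomisation is stratified by gender only, so the design does not balance function either.

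At stake is a modest amount of precision. The choice has to be fixed before unblinding to be credible.

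**Working it through.** **1. Can baseline IADL vary?** Among participants admitted on the functional limb it is 0 by definition, with at most one item minimally changed. Among those admitted on the MoCA limb it need not be 0. The focal-deficit ground for excluding dementia also does not require intact function. So IADL can vary, but the document does not say in how many participants.

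**2. The plan's own sample size figure.** The Sample size section gives 31% decline, an odds ratio (OR) of 4, two-sided 5% (sidedness assumed), 80% power and 117 per arm. The odds at 31% are 0.31/0.69 = 0.449; divided by 4 they are 0.112, a risk of 10.1%. The pooled two-proportion formula for 31% vs 10.1% gives 58 per arm, not 117. For 31% vs 15.5% (OR about 2.4) it gives 116. That mismatch is a separate matter. Here it means that two treatment effects should be tried at 117 per arm: the stated OR of 4, and an assumed OR of 2.4, which gives power near the nominal 80%.

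**3. Closed-form gain from a binary IADL covariate.** Assumed: prevalence *q* of IADL loss and odds ratio *g* between IADL loss and decline. Neither is in the document. Power = Φ(|β|/SE − 1.96).

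Worked case, *q* = 30%, *g* = 3, treatment OR 2.4 within IADL strata, control risk 31% overall:
- Control risks are 23.7% (IADL 0) and 48.2% (IADL > 0); 0.7 × 23.7 + 0.3 × 48.2 = 31.0%.
- Intervention risks are 11.4% and 27.9%; 0.7 × 11.4 + 0.3 × 27.9 = 16.4%.
- Without IADL: β = 0.831, SE = √[1/(117 × 0.31 × 0.69) + 1/(117 × 0.164 × 0.836)] = 0.320, power = Φ(0.64) = 73.8%.
- With IADL: β = ln 2.4 = 0.875, SE = 0.329 from the inverse information matrix, power = Φ(0.70) = 75.8%.
- Gain: 2.0 points.

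Gains in power points over the assumed range:

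| Prevalence of IADL loss | Treatment OR 2.4: IADL OR 2 / 3 / 5 | Treatment OR 4: IADL OR 2 / 3 / 5 |
|---|---|---|
| 5% | 0.2 / 0.5 / 1.2 | 0.1 / 0.2 / 0.4 |
| 10% | 0.4 / 1.0 / 2.3 | 0.1 / 0.3 / 0.7 |
| 20% | 0.6 / 1.7 / 3.9 | 0.2 / 0.5 / 1.3 |
| 30% | 0.8 / 2.0 / 4.6 | 0.2 / 0.6 / 1.6 |
| 50% | 0.8 / 2.0 / 4.0 | 0.2 / 0.6 / 1.4 |

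If everyone has IADL = 0, the covariate is constant and the gain is exactly 0.

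**4. Against the model actually planned.** The planned model already contains MoCA, age and education. A simulation put one normal score standing for these in both models (assumed log-odds 0.8 per SD, latent correlation 0.3 with IADL), with 117 per arm, 31% control risk and a single 12-month outcome. The repeated-measures structure was not modelled.

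At treatment OR 2.4 (3,000 runs per setting; 8,000 where marked *):
- IADL OR 2, prevalence 5-20%: −0.4 to +0.2 points, which is simulation noise; prevalence 25%*: +0.5.
- IADL OR 3, prevalence 30% and 50%: 69.9% to 72.0% (+2.1) and 71.4% to 73.9% (+2.5); prevalence 25% and 40%*: +2.4 and +2.6.
- IADL OR 5, prevalence 25% and 40%*: +4.7 and +5.0, with a Monte Carlo standard error of about 0.35.

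At the stated treatment OR of 4, power is already about 95-97%. The gain is below 1 point at IADL OR 2 to 3, and about 2 points at IADL OR 5.

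**The case against.** The strongest case against is that this is a preference, not a defect. A prespecified covariate list is a legitimate choice, the sample size does not rely on adjustment, and a similar remark could be made about the Rankin score, depressive symptoms or lesion load. The functional entry limb makes IADL nearly constant for those who enter by it. The exclusion of dementia narrows the range for the rest. No figure in the protocol shows that baseline IADL predicts decline.

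Most of this stands. What remains is that IADL, unlike an arbitrary baseline variable, measures a component that the protocol builds into the outcome, and the *or* in Criteria B leaves it free to vary.

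Four stronger readings are tempting and not supported:
- **That the comparison is biased.** Omitting a baseline covariate does not bias a randomised comparison. A chance imbalance of 10 points or more in IADL loss (about 8-13% of randomisations at prevalence 25-40% and 112 per arm, from SD = √[2p(1−p)/112]) is ordinary sampling variation, which the confidence interval already covers.
- **That power is shown to be lost.** The gain may be zero; the inputs that decide this are not in the document.
- **That power would rise from about 79% to as much as 86%.** That arises only by comparing with a wholly unadjusted model, at an assumed 15.5% intervention risk and an IADL odds ratio of 8. The planned model is not unadjusted, and neither figure is in the protocol.
- **That a person with IADL loss at entry needs less further change to be classed as declined.** This is plausible, but the status diagnosis is made "according to clinical, neuropsychological, and functional criteria" with no IADL threshold stated.

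**Conclusion.** The point holds as a small improvement, not as an error. The text establishes that function enters the primary outcome, that baseline IADL can vary and is collected, and that it is absent from the fixed covariates. It does not establish how much is gained. Over the planned MoCA-adjusted model, and at a treatment odds ratio of about 2.4, the gain is about 0 to 2.5 power points for an IADL odds ratio of 2 to 3. It reaches about 4 to 5 points only for an odds ratio of 5 with roughly 25-40% affected. It is nil if nearly all enter with IADL = 0, and small at the stated treatment odds ratio of 4. The IADL prevalence, its association with decline, the treatment odds ratio of 2.4 and the overlap with MoCA are all assumptions.

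**What to change.** Optional: in Data analysis, add baseline IADL, scored as for entry (0 vs above 0, or number of items changed), to the prespecified covariates of the primary GEE logistic model, beside baseline MoCA. Otherwise, say in a sentence why function is left out.

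The cost is one degree of freedom and no new data. The simulations showed no loss of power beyond noise when IADL was weakly informative. The treatment odds ratio would then be conditional on IADL as well and should be reported as such: in the worked case it is 2.4, against 2.3 (e^0.831) without the covariate. If IADL proves to be 0 for every participant at baseline, the term drops out; state that rule in advance. The change should be made before unblinding.

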#### Exclusion criteria

Subjects cannot be included if they have at least one of the following: 1) a diagnosis of dementia; 2) stroke with formal indication for physiotherapy or speech therapy, or Rankin score ≥ 2; 3) any contraindication for walking, physical limitation to gait (orthopaedic or of other structural causes) that compromises physical activity, or other condition potentially interfering with the active treatment (e.g. severe arthritis or severe musculoskeletal pain associated with walking); 4) evidence of neurodegenerative disease (of aetiology other than vascular), severe mental disorder (e.g. major depressive episode or psychosis) or medical disease which could significantly interfere with the subjects’ participation or with their quality of life (e.g. cancer, congestive heart failure, or unstable angina).

### Study outcomes

The primary outcome measure will be cognitive decline defined as a dichotomous variable (decline/no decline) through cognitive status criteria as described in the Assessments section below. The secondary outcomes are changes in neurocognitive scores of at least 1.5 standard deviation (SD) from baseline to endpoint (using *z* scores), a decline in the raw values of neuropsychological tests, in quality of life, functional and motor status, and falls.

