The World Health Organization (WHO) (2010) [9] and the American College of Sports Medicine (2017) [10] have produced recommendations on physical activity. The associations of cardiovascular [11] and cerebrovascular diseases [12] also produced recommendations on physical activity for cardiac and for stroke patients, respectively. However, data on cognitive disorders are quite controversial. Recent observational studies suggested that physical activity could prevent the progression of VCI [13]. On the other hand, a recent review found no protective effect of physical activity in cognitive decline [14]. In the DAPA trial published recently, no beneficial effect was achieved with physical activity in patients with Alzheimer’s disease [15]. There have been intervention trials in patients at high vascular risk without previous stroke but, with the exception of one study [16] (which did not include VCI), no benefit was found [17, 18].

Given these contradictory findings, we lack a robust evidence base to recommend physical activity in VCI. Furthermore, there are no data on what type, intensity, and frequency of activity would be necessary to achieve long-term gains.

We aim to test, through a randomised controlled trial (RCT), if physical activity has a beneficial impact on VCI. We hypothesise that regular physical activity of moderate intensity for at least 6 months will improve cognitive impairment in subjects with cognitive impairment due to cerebrovascular pathology.

We also aim to evaluate the effect of physical activity on the quality of life, and on functional and motor status.

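### One secondary cognitive outcome is a 1.5 SD change with no direction; it should be worded as decline and kept as support for a continuous composite z score

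*Protocol article*

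**What the plan says.** Study outcomes in the protocol article first fixes the primary outcome as decline versus no decline in cognitive status. It then lists secondary outcomes, starting with "changes in neurocognitive scores of at least 1.5 standard deviation (SD) from baseline to endpoint", based on z scores. The same sentence continues with "a decline in the raw values of neuropsychological tests, in quality of life, functional and motor status, and falls". The first item has a threshold and no direction; the second has a direction and no threshold.

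The Background gives the hypothesis as an improvement: physical activity "will improve cognitive impairment in subjects with cognitive impairment due to cerebrovascular pathology".

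Data analysis describes the neuropsychological endpoint differently again, as "change in neuropsychological evaluation through composite or global scores", assessed from baseline to 6 and 12 months. On the model it says: "For secondary outcomes, logistic or linear regression analysis will be used as applicable". The covariates it names are age, gender, education and baseline MoCA. It also says: "Observing a statistically significant difference on any of the outcomes will be considered preliminary evidence of efficacy".

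**The concern.** There are two separate weaknesses.

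1. **No direction.** An outcome that counts any change of 1.5 SD or more treats a large gain and a large loss alike. A treatment that lowers losses and raises gains moves the two parts of the count in opposite directions. The pooled proportion can then show no difference, or a higher rate of change in the arm that benefits.
2. **The cut itself.** Even if only declines count, the z score is reduced to yes or no at a point that few participants may cross, and the graded information is lost.

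The item is secondary, but it is not idle. Under the rule in Data analysis, significance on any outcome counts as preliminary evidence of efficacy. The primary outcome is itself binary, so graded information on cognition has to come from the neuropsychological scores. The article offers several forms of these (thresholded z score, raw values, composite or global change) and does not say which one leads.

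**Working it through.** **No plan figure to reproduce.** The sample size in the article was calculated for the primary outcome. It gives no SD of change, mean change or effect for this outcome, so those inputs below are assumptions.

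**Inputs**
- From the article: 280 randomised 1:1 with 20% loss, so 280 × 0.8 / 2 = 112 per arm; alpha 0.05, taken as two-sided (1.96).
- Assumed: normally distributed change; benefit e = 0.3 SD; test-retest correlation r = 0.6 to 0.8; control drift m = 0 to -0.5 SD; sample SD of the z score = 1.

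**Step 1: the literal rule can cancel a benefit.** Take SD of change 1.0, m = -0.2 and, for this example, e = 0.4. Mean change is -0.2 in controls and +0.2 in the intervention arm.
- Loss of at least 1.5: Φ(-1.5 + 0.2) = 9.7% in controls; Φ(-1.5 - 0.2) = 4.5% in the intervention arm.
- Gain of at least 1.5: 4.5% in controls; 9.7% in the intervention arm.
- Either direction: 14.1% in both arms (unrounded 14.14%).

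Declines are halved and the outcome shows no difference.

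**Step 2: formulas for power**
- SD of change: s = √(2(1 - r)).
- Decline: control p1 = Φ((-1.5 - m)/s); intervention p2 = Φ((-1.5 - m - e)/s).
- Two proportions, with p̄ = (p1 + p2)/2: power = Φ((|p1 - p2| - 1.96√(2p̄(1 - p̄)/n)) / √(p1(1 - p1)/n + p2(1 - p2)/n)).
- Continuous, adjusted for own baseline: power = Φ(0.3/(√(1 - r²) × √(2/112)) - 1.96).

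Example with r = 0.7 and m = -0.5: s = √0.6 = 0.775. p1 = Φ(-1.0/0.775) = 9.8% and p2 = Φ(-1.3/0.775) = 4.7%, so decline-only power is 32%. The continuous power is Φ(0.3/(0.714 × 0.1336) - 1.96) = 88%.

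**Step 3: results at 112 per arm, sample SD of the z score = 1**

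| r | drift | decliners, control vs intervention | power, decline only | power, either direction | power, continuous |
|---|---|---|---|---|---|
| 0.6 | 0 | 4.7% vs 2.2% | 17% | 7% | 80% |
| 0.6 | -0.5 | 13.2% vs 7.3% | 30% | 16% | 80% |
| 0.7 | 0 | 2.6% vs 1.0% | 15% | 8% | 88% |
| 0.7 | -0.5 | 9.8% vs 4.7% | 32% | 21% | 88% |
| 0.8 | 0 | 0.9% vs 0.2% | 10% | 9.5% | 96% |
| 0.8 | -0.5 | 5.7% vs 2.0% | 30% | 25% | 96% |

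At intermediate drift the either-direction power falls further, to about 4% (r = 0.6, m = -0.2). At zero drift, what either-direction power there is comes from more change in the intervention arm. Control decliners number roughly 1 to 15 of 112. At the low end the normal approximation is poor, so the 10% is only indicative.

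**Step 4: sensitivity to the z-score reference.** The article does not say whether z scores refer to the sample or to norms. Suppose they are norm-based and the sample SD is 1.5 or 2 norm units, with drift and benefit unchanged in sample SDs. The cut then sits at 1.5/1.5 = 1.0 or 1.5/2 = 0.75 sample SD.
- Lowest power (SD 1.5, r = 0.8, no drift): Φ(-1.0/0.632) = 5.7% vs Φ(-1.3/0.632) = 2.0%; power about 30%.
- Highest power (SD 2, r = 0.8, drift -0.5): Φ(-0.25/0.632) = 34.6% vs Φ(-0.55/0.632) = 19.2%; power about 75%.

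Control decline rates now run from about 6% to 39%. The continuous analysis is unchanged at 80 to 96% and remains higher for every combination: at the most favourable point for the cut it is 96% against about 75%.

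**The case against.** The other side has a good case on impact.

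- **A continuous analysis is already within the plan.** Raw test values and composite or global score change are both listed, the latter at 6 and 12 months, with linear regression allowed. A reader might infer that the neuropsychological battery is bound to read as null or be uninterpretable. The documents do not support that: the same tests are also to be reported in forms without the cut.
- **Decline was probably meant.** The primary outcome is decline, and the next item in the same sentence says so too. Change is also the article's general word for its secondary outcomes. A reader might infer that pooling gains with losses was intended; nothing in the article says that. Still, the stated hypothesis is improvement, so context does not settle the direction.
- **The model is not really left open.** The phrase "logistic or linear regression analysis will be used as applicable" most naturally means logistic for binary and linear for continuous outcomes. It should not be read as an unresolved choice for this item.
- **Some detail belongs in the SAP**, which is not shown. The z-score reference, the choice of tests and own-baseline adjustment may be there, so their absence from the article is no fault. The outcome definition itself, however, is printed in the article with a threshold and no direction.
- **Scale and status.** Being listed first implies no hierarchy, the trial was not sized for this item, and a threshold proportion beside a continuous score is a recognised way to show clinical relevance. Norm-based z scores could also make the event much less rare (step 4).

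These points limit the consequence. They do not supply the missing direction or remove the loss of power from the cut.

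**Conclusion.** The point holds in a limited form. One secondary cognitive outcome lacks a direction and, read literally, can hide a benefit completely, as the 14.1% versus 14.1% example shows. Read as decline only, it is clearly less powerful than a continuous analysis of the same score: illustratively 10 to 32% against 80 to 96% at 112 per arm for a 0.3 SD benefit. The decline figure is about 30 to 75% if z scores are norm-based and the sample SD is 1.5 to 2. All of these rest on assumed SD, correlation, drift and effect. The ordering is firmer than the individual figures, since the continuous form is ahead in every combination examined.

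This does not touch the primary outcome and does not invalidate the secondary cognitive results as a whole. It is an inexpensive improvement worth making before the data are analysed, because the article leaves open which form of the neuropsychological result leads while allowing any significant outcome to support efficacy.

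**What to change.** 1. Reword the threshold outcome as a decline of at least 1.5 SD, or report decline and gain of at least 1.5 SD as two separate proportions. Keep it as a supportive, descriptive result.
2. Name the continuous composite z score at 6 and 12 months as the main analysis of this secondary outcome, in a linear model adjusted for its own baseline value. Baseline MoCA, the only baseline score among the named covariates, can stay. Treat the individual tests in the same way.
3. State there whether z scores refer to the sample or to norms, if the SAP does not already do so.

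The cost is outcome wording and SAP text; the scores are already collected at all three visits. The downside is that a mean z-score difference is less intuitive than a proportion, which is why the proportion is still reported.
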